#### Current Treatment for Aromatase Inhibitor-Induced Joint Pain

Non-steroidal anti-inflammatory drugs (NSAIDs), the most common medications used to treat pain associated with arthritis, may lead to serious renal and gastrointestinal toxicity, particularly in older adults. (76, 77) Selective cyclooxygenase-2 (COX-2) inhibitors, such as rofecoxib and celecoxib, are effective analgesics with fewer gastrointestinal side effects but have recently been shown to elevate the risk of cardiovascular events. (78) Non-toxic treatments that effectively relieve AI-induced musculoskeletal pain are needed. Ongoing studies are evaluating the potential benefits of physical activity, vitamin D, glucosamine/chondroitin and omega-3 fatty acids for treating this toxicity.

Since research in this area is limited, a small pilot study evaluating the use of acupuncture to relieve symptoms of AI-associated arthralgias was initially conducted. In this study of 21 women treated with a 6-week course of total body and auricular acupuncture, improvements were reported in pain severity, pain-related functional outcomes, and physical well-being, and no significant adverse events were reported. (79) This study was limited due to its small sample size and lack of an adequate control group. Investigators then went on to conduct a randomized, blinded, sham-controlled study in 38 breast cancer patients with AI-associated arthralgias. (80) True acupuncture for 6 weeks was associated with about a 50% decrease in mean BPI-SF scores compared to sham acupuncture with superficial needling at non-acupuncture points. Similar findings were seen for the WOMAC and M-SACRAH scores. Results found that acupuncture is an effective and well-tolerated strategy for managing this common treatment-related side effect.

#### Acupuncture for the Treatment of Joint Pain

Approximately 25% of the population over the age of 55 years are affected by joint pain and about half of them will have some restriction of normal daily activities. (59, 81) Virtually all individuals over the age of 65 have radiographic evidence of osteoarthritis. (82) With

conventional approaches such as analgesics and exercise, controlling pain and minimizing loss of function are the principal aims of treatment. (83, 84) About two-thirds of individuals who suffer from joint pain have used complementary and alternative treatments to control their symptoms. (85) However, due to the dearth of rigorously derived experimental evidence, most third party payers do not reimburse patients for the cost of many of these procedures.

Acupuncture is a traditional Chinese method of medical treatment involving the insertion of fine, single-use, sterile needles in acupoints according to a system of channels and meridians that was developed by early practitioners of Traditional Chinese Medicine (TCM) over 2000 years ago. The needles are stimulated by either manual manipulation, electrical stimulation, or heat. (86) Patients in pain have imbalance in their Qi or vital energy. The Qi travels through 12 main meridians in the body, connecting the body in a weblike matrix. (87) Within the traditional framework, meridians are thought to represent conduits for electrical signals. (88) During traditional acupuncture, needles are inserted into a meridian point and then manipulated to elicit "de qi." *De qi* has been described as a sensation of achiness, soreness, or dull pain. According to TCM, elicitation of *de qi* re-establishes normal flow of Qi and is essential for clinical efficacy. More recently, it has been postulated that sensation of *de qi* represents activation of nerve receptors during insertion of acupuncture needles at the appropriate location and depth of traditional acupuncture points. (89) Currently, acupuncture is often used with TCM and it is a recognized health profession with strict licensure and regulatory status in 40 states. (90)

Acupuncture is a popular non-pharmacological modality used for treating a variety of conditions, including musculoskeletal pain. Acupuncture has been shown to have short-term analgesic effect in musculoskeletal pain. (91, 92) Clinical trials have found a benefit to patients with knee osteoarthritis when acupuncture is used as an adjunct to conventional management strategies. (93) In a randomized study of 97 patients with osteoarthritis of the knee, acupuncture as a complementary therapy to pharmacological treatments is more effective than pharmacological treatment alone, in terms of reducing pain, improving physical function and health-related quality of life. (94) A trial conducted in Germany concluded that true acupuncture has a better effect than sham acupuncture in the treatment of knee and back pain. (95) However, in two large multicenter trials of acupuncture for osteoarthritis of the knee, one found a benefit in joint pain and function compared to sham acupuncture and the other found no additional improvement in pain scores. (96,97)

Acupuncture and TCM vary slightly from Western biomedicine in the methods of physical examination, evaluation and diagnostic criteria. For example, the major diagnostic criteria of TCM practitioners include inquiry, inspection of the body, acupuncture channels or meridians, and the tongue, as well as palpation of the channels, points and pulse. Pulse palpation in TCM occurs at the radial artery in the wrist and is assessed for rate, rhythm, force and shape, which all correspond to internal physiological processes according to TCM theory. Using these criteria, a differential diagnosis is made and an appropriate point prescription is applied as treatment.

Acupuncture points are located on the body using anatomical locations and the TCM standard unit of body measurement termed the "cun." As everyone's body has different dimensions, a cun is defined according to the person whose body is to be treated. For example, 1 cun is equivalent to the width of the thumb, in the middle, at the crease; 3 cun is equivalent to the combined breadth of the 4 fingers, at the level of the pinky finger's first joint above the palm of the hand; and 12 cun is equivalent to the distance from the elbow crease to the wrist crease.

Auricular acupuncture therapy has long been used in China to treat conditions by stimulating certain points on the ear with needles. The history of its use has been documented in various historical texts and auricular therapy is maintained in common use in the present day system of acupuncture. The National Acupuncture Detoxification Association (NADA) protocol has been extensively studied for its effect on addiction and stress relief. This protocol is endorsed by the National Institute on Drug Abuse (NIDA), the governing body of the treatment of chemical dependency, and is being used in some states such as Florida and California within their drug rehabilitation and court systems. (98-100) The function of the NADA protocol with full body acupuncture treatment is to relieve pain and decrease stress.

The most common presentation of musculoskeletal pain according to TCM is “Bi Syndrome.” “Bi” means obstruction or blockage. “Bi Syndrome” describes a set of patterns in which obstruction of qi and blood through the channels causes pain. Qi and blood are defined as the basic elements of all physiological activity according to TCM. The TCM differential diagnosis of “Bi syndrome” encompasses several disorders known in Western biomedicine, such as osteoarthritis, rheumatoid arthritis, rheumatic fever, fibromyalgia, gout and sciatica. (101-103) Of interest to this study, AI-induced musculoskeletal pain follows the pattern diagnosis of “Bi syndrome.”

The use of complementary and alternative medicine (CAM) is growing in the U.S. According to a Center for Disease Control (CDC) report of the 2002 National Health Interview Study, 75% of respondents reported using some form of CAM. (104) Breast cancer patients are the cancer group most likely to use CAM therapies in conjunction with their conventional treatment. (105-107) Therapies used include nutritional and herbal supplements, massage, dietary changes, prayer, yoga and acupuncture. (108-110) An increasing amount of evidence suggests that acupuncture has a role in the supportive care of cancer patients for treating chemotherapy-induced nausea and vomiting, xerostomia, leukopenia, and other chemoradiotherapy-induced symptoms. (111-116) A recent study found that acupuncture treatments given twice weekly for 4 weeks, then weekly for 8 weeks (12 weeks total) was as effective as the antidepressant, venlafaxine, for managing vasomotor symptoms related to hormonal therapy in breast cancer patients. (117) In fact, acupuncture had a more durable effect with fewer side effects compared to venlafaxine and had additional benefits, including increased sex drive, improved energy and sense of well-being.

#### Mechanism of Action of Acupuncture

Ideally, relief from AI-associated arthralgia should be through non-hormonal mechanisms, so as not to interfere with the efficacy of the drug. Acupuncture is under current investigation for its mechanistic effect within the biomedical research paradigm and its influence on particular conditions or symptom sets. Although the precise mechanism of action is unknown, acupuncture analgesia is thought to be mediated by central mechanisms of pain control through the release of specific neurotransmitters, such as endorphin. (118-120) A recent study suggested that acupuncture modulates pain signals in the central nervous system at the level of the spinal cord, midbrain and cortex via release of endogenous opiates and neurotransmitters. (121, 122) Early studies show that naloxone, an antagonist to opiates, attenuated the analgesic effects of acupuncture in humans and mice. (120, 123) In humans after receiving acupuncture, elevated levels of  $\beta$  endorphin in the cerebrospinal fluid have been observed. (119) Animal studies with electro-acupuncture (EA) have shown that EA at low frequency of 2 Hz stimulates the release of  $\beta$  endorphins, enkephalin and endomorphin, which activates  $\mu$  and  $\delta$  opiate receptors. (124) In addition, EA at higher frequency stimulates release of dynorphin which activates the  $\kappa$  opiate receptors. (125)

Another proposed mechanism of acupuncture analgesia involves the serotonergic pathway. Acupuncture has been shown to activate the release of serotonin from the serotonergic raphe spinal neurons in the nucleus raphe magnus, which is associated with the descending pain inhibitory pathway. (126) Serotonin then binds serotonin receptors on inhibitory interneurons in the spinal cord to release enkephalin, which inhibits pain sensation signals. (127) A more recent study in rats found that acupuncture activate neurons in the periductal gray matter of the midbrain, a region in the brain that contributes to the descending pain inhibitory pathway. EA also had an anti-nociceptive effect by abolishing histamine and dopamine release induced by pain stimuli. (128) More recently, researchers are looking at the anti-hyperalgesic effect of acupuncture in inflammatory mouse models. In one *in vivo* study employing a persistent inflammatory pain rat model, administration of EA increased paw withdrawal latency suggestive of anti-hyperalgesic effect. In addition, EA was able to reduce inflammatory paw edema in the rats. (129, 130)

### Sham Acupuncture Interventions

The optimal control group for studies of acupuncture is controversial. Sham acupuncture methods include acupuncture for an unrelated condition, needle insertion at nonacupoint locations, noninsertive simulated acupuncture, or use of retractable needles. However, most acupuncture controls are not completely inert. Potential benefits may be conferred from the physiologic effect of needling even when not performed according to established principles. (131-134) Detrimental effects from sham needling are also possible, and other studies have found no benefit in the sham group. (134)

In the prior sham-controlled study of acupuncture for AI-related joint symptoms, the sham intervention used superficial needle insertion at body locations not recognized as true acupoints. (80) Results showed that 22% of subjects who received sham acupuncture reported at least a 2-point decrease in BPI-SF worst pain scores, consistent with the literature that reports a 25-55% placebo effect for nonacupoint and superficial insertion sham methods. (135) In this study, 57% of patients in the sham group believed they were receiving true acupuncture, suggesting that blinding was effective. For the auricular acupuncture, the sham intervention will involve adding adhesives to the selected points on the helix of the auricle. While a sham auricular intervention was not applied in the prior study, investigators feel that application of the sham auricular intervention may increase the effectiveness of blinding. While future studies may attempt to look at other point protocols and acupuncture interventions oriented in other traditional theories, investigators feel that it is important to remain consistent in this study design. Moreover, investigators will control for a placebo effect based on previous research as reflected in the statistical methods.

### Patient Reported Outcomes for Joint Symptoms

This study will rely on a patient-reported outcome (PRO) for the primary endpoint. Traditionally, the Food and Drug Administration (FDA) requires substantial evidence for reaching a conclusion that a drug or intervention will have an effect on a given condition. Evidence that shows not only a change in symptoms, but how that change translates to other specific endpoints, such as the patients' ability to perform activities, is sometimes required by the FDA for approval. (136) The PRO of symptomatic and functional improvement may benefit from the use of objective measures, such as magnetic resonance imaging (MRI) of joints to assess for structural changes or functional assessments, including grip strength. (22)

Studies assessing AI-induced arthralgias have shown a correlation between PROs and objective findings. Morales et al. demonstrated that the subjective symptoms of AI-induced arthralgias in the hands are associated with physiologic changes to the joint and functional impairments. (22) The patients in this study were assessed with serial MRIs of the hands, measurements of grip strength, and symptoms self-assessments. In a 6-month period, women taking AIs were more likely than those on tamoxifen to have an increase in tenosynovial changes as seen on MRI, a decrease in grip strength as measured by a sphygmomanometer, as well as increased pain and stiffness as measured by self-administered questionnaire. (22)

Since there are no well-validated measures specifically for AI-induced arthralgias, scales that captured joint pain, stiffness, and functional status in the hips and knees (WOMAC) and hands (M-SACRAH) were selected, and a general pain scale used in cancer patients (BPI-SF). The BPI-SF (137) is a 14-item questionnaire which asks patients to rate pain over the prior week and the degree to which it interferes with activities on a 0 to 10 scale. Numeric rating scales such as the BPI are among the most common, valid, and reliable measures used to assess cancer pain. (138) The Western Ontario and McMaster Universities Osteoarthritis Index (WOMAC) Version 3.1 is a validated measure for assessing osteoarthritis of the knees or hips and consists of 24 questions related to three subscales: pain, stiffness, and physical function. (139) The Modified-Score for the Assessment and Quantification of Chronic Rheumatoid Affections of the Hands (M-SACRAH) consists of three domains assessing pain, stiffness, and functional status in patients suffering

from hand osteoarthritis and rheumatoid arthritis. (140) Well-validated quantitative functional testing with grip strength to assess hand function and the “Timed Get Up and Go” (TGUG) test to assess functional status in the lower extremities have also been included. (141,142)

### Acupuncture for Aromatase Inhibitor-Related Arthralgias

Researchers at CUMC have extensive experience evaluating interventions for the treatment of AI-induced arthralgias. Since research in this area is limited, a small pilot study evaluating the use of acupuncture to relieve symptoms of AI-associated arthralgias was initially conducted. In this study of 21 women treated with full body and auricular acupuncture twice weekly for six weeks, improvements were reported in pain severity, pain-related functional outcomes, and physical well-being, and no significant adverse events were reported. (79) Another pilot study used electro-acupuncture administered twice weekly for 2 weeks followed by 6 weekly treatments in 12 breast cancer survivors with AI-related arthralgia. (143) Similarly, the patients reported significant reductions in pain severity, stiffness, and joint symptom interference according to the BPI. Subjects also reported a significant decrease in fatigue and anxiety. These studies were limited due to small sample sizes, unblinded interventions, and lack of an adequate control group.

A randomized, blinded, sham-controlled study in 38 women with early stage breast cancer and AI-induced arthralgias to assess the efficacy of acupuncture was then conducted. As is shown in Figure 1, a 6-week course of true acupuncture was associated with about a 50% decrease in mean BPI-SF scores. No change from baseline was observed for the sham arm. At 6 weeks, the mean BPI-SF worst pain scores (range, 0-10) were lower for true acupuncture compared to sham acupuncture (3.0 vs. 5.5,  $p<0.001$ ), as well as pain severity (2.6 vs. 4.5,  $p=0.003$ ) and pain-related interference (2.5 vs. 4.5,  $p=0.002$ ). Similar findings were seen for the WOMAC and M-SACRAH scores which assess knee/hip and hand joint symptoms, respectively. (144) These measures were very effective at capturing the symptoms of AI-related arthralgia.

**Figure 1.** Percent change in the group mean Brief Pain Inventory-Short Form (BPI-SF) scores from baseline to 3 and 6 weeks for the true and sham acupuncture groups: A) BPI-SF worst pain, B) BPI-SF pain severity, and C) BPI-SF pain-related interference.

[figure not shown]

### Summary

Due to early detection and improved treatments, women with breast cancer are living longer. The increase in breast cancer survival is largely due to the benefits of hormonal therapy, such as tamoxifen and aromatase inhibitors (AIs), for the treatment of hormone-sensitive breast cancer. Recent clinical trials have demonstrated that AIs are more effective than tamoxifen at reducing breast cancer recurrences. (8-13) However, breast cancer patients receiving AIs have a higher incidence of osteoporosis, bone fractures and musculoskeletal symptoms, particularly joint pain and stiffness. Musculoskeletal pain, which occurs in up to 50% of patients treated with AIs (18), may lead to noncompliance, deterioration of quality of life due to physical disability, sleep disturbance, impaired cognitive function, depression and anxiety, and increased utilization of health care resources. (73-75) Since women with hormone receptor-positive breast cancer require long-term hormonal therapy, an important objective is minimizing long-term side effects to enhance patient compliance and improve quality of life. Therefore, targeted interventions that relieve AI-induced musculoskeletal pain are needed.

There are currently no proven treatments for AI-induced arthralgias. Acupuncture is a popular non-pharmacologic modality that has been shown to have analgesic effects in many chronic pain syndromes, including osteoarthritis. A recent evaluation of acupuncture by the National Institutes of Health concluded that it is a useful adjunct in a range of painful conditions, including musculoskeletal pain. (145) While the use of complementary and alternative medicine for the treatment of persistent musculoskeletal pain continues to increase, rigorous clinical trials examining their efficacy are needed before definitive recommendations can be made. Investigators recently conducted a randomized, blinded, sham-controlled trial to assess the effect of acupuncture on musculoskeletal pain induced by AIs. The true acupuncture group had about a 50% decrease in mean BPI-SF worst pain score compared to the sham acupuncture group (3.0 vs 5.5,  $p < 0.001$ ). (80) There were also differences in pain severity and pain related interference. Acupuncture was well tolerated with no complications. However, despite these promising results, this single institution study had a relatively small sample size, had a single acupuncturist, and was only a 6-week intervention. (80) For the community, cost and lack of insurance coverage limit access to this therapy. A larger, confirmatory, multicenter trial is necessary to truly control for confounding factors, and may provide the data critical to extend coverage for this indication. This approach is innovative because it is a new application of a well recognized pain therapy for breast cancer supportive care. Improved adherence is critical for this class of medications, given the large discontinuation rate due to toxicity, which has been shown to affect survival. (17)

For this current proposal, SWOG will conduct a multicenter randomized, blinded, sham- and waitlist-controlled clinical trial to test the effect of acupuncture on AI-associated joint pain in 228 postmenopausal women with early stage hormone receptor-positive breast cancer who report joint pain that has increased or started since initiation of AI therapy. The primary endpoints are to compare the mean BPI-SF worst pain scores at 6 weeks in the true acupuncture compared to sham acupuncture and waitlist groups in order to confirm initial results of a 6-week acupuncture intervention given twice weekly in a larger multicenter study. Secondary exploratory endpoints include evaluations at 12, 24, and 52 weeks to determine the benefit of additional 6 weekly acupuncture treatments for maintenance and to determine the durability of response 12 and 40 weeks after stopping acupuncture, respectively. This study will be the first large multicenter trial to investigate the effect of acupuncture in treating AI-induced joint symptoms in breast cancer patients. This is a common complaint in this patient population which can lead to the discontinuation of a life-saving therapy. Research has shown that even taking this medication less than 80% of the time can have a negative impact on survival. (17) Results from this study will inform clinicians, insurance companies and patients on whether or not this is an effective therapy, and may help predict who is most likely to benefit from this therapy.

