### 1.2 Secondary objectives are to investigate the effects of true acupuncture administered twice weekly for 6 weeks (8-12 sessions) followed by 6 weekly treatments (4-6 sessions) of maintenance (12-18 sessions total over 12 weeks) compared to sham acupuncture and waitlist control in this study population. The evaluations at 12 and 24 weeks are to determine the benefit of additional 6 weekly acupuncture treatments for maintenance and to determine the durability of response after stopping acupuncture, respectively. The evaluation at 52 weeks is to determine the long-term effects of acupuncture and adherence to AIs.

- a. To evaluate the effects of acupuncture on the Brief Pain Inventory-Short Form (BPI-SF) worst pain, worst stiffness, pain severity, and pain-related interference scores at 6, 12, 16, 20, 24, and 52 weeks.
- b. To evaluate the effects of acupuncture on Western Ontario and McMaster Universities Osteoarthritis (WOMAC) index (pain, stiffness, and function) for the hips and knees at 6, 12, 24, and 52 weeks.
- c. To evaluate the effects of acupuncture on Modified-Score for the Assessment and Quantification of Chronic Rheumatoid Affections of the Hands (M-SACRAH) (pain, stiffness, and function) at 6, 12, 24, and 52 weeks.
- d. To evaluate the effects of acupuncture on the PROMIS Pain Impact-Short Form (PROMIS PI-SF) at 6, 12, 24, and 52 weeks.
- e. To evaluate the effects of acupuncture on quality of life (QOL) as assessed by the Functional Assessment of Cancer Therapy-Endocrine Subscales (FACT-ES) at 6, 12, 24, and 52 weeks.
- f. To evaluate the effects of acupuncture on functional testing with grip strength and "Timed Get Up and Go" (TGUG) test at 6, 12, 24, and 52 weeks.
- g. To evaluate the effects of acupuncture on analgesic and opioid use at 2, 4, 6, 12, 16, 20, 24, and 52 weeks.
- h. To evaluate the effects of acupuncture on self-reported AI adherence at 12, 24, and 52 weeks.
- i. To assess AI adherence via urine AI metabolites at baseline, 24, and 52 weeks.
- j. To evaluate the effects of acupuncture on serum hormones (estradiol, FSH, LH) and inflammatory biomarkers (serum TNF $\alpha$ , IL-6, IL-12, CRP and urine CTX-II) at 6, 12, and 24 weeks.
- k. To evaluate whether polymorphisms in *CYP19A1* aromatase gene predict severity of AI-related joint symptoms.
- l. To assess the safety and tolerability of acupuncture in this study population.

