#### 7.6 Acupuncture Treatment

##### a. Acupuncture Schedule

Patients will be randomized (2:1:1) to true acupuncture vs. sham acupuncture vs. waitlist control. Patients will be blinded to true acupuncture vs. sham acupuncture. Patients will not be blinded to the waitlist control. The study intervention is to begin within 5 working days of registration.

- True acupuncture administered twice weekly for 6 weeks followed by weekly treatments for 6 weeks (12-18 sessions total over 12 weeks).
- Sham acupuncture administered twice weekly for 6 weeks followed by weekly treatments for 6 weeks (12-18 sessions total over 12 weeks).
- Duration of intervention – Study intervention will be continued for 12 weeks unless unacceptable toxicity occurs, the subject has concurrent illness that necessitates withdrawal or subject decides to withdraw from participation for any reason. If the subject’s medical condition is influenced by the knowledge of which study intervention she was assigned, there will be unblinding upon the Investigator’s request.

- A licensed Study Acupuncturist(s) designated at each site will administer the true and sham acupuncture treatments.
- After the 24-week visit, all patients will receive a voucher for 10 free true acupuncture sessions administered by the Study Acupuncturist(s) and to be used at the patient's convenience and documented in the web-based calendar.

During the first 6 weeks of acupuncture, the twice weekly acupuncture sessions should be at least 24 hours apart and if a session is missed, it may be made up the following week for up to 3 sessions per week. The schedule will be flexible to allow for 8-12 sessions during the first 6 weeks, which may be more reflective of what may happen in the "real world" setting. During the second 6 weeks of weekly maintenance acupuncture, there will be no make-up of missed sessions, so patients may have only 1 session per week during the second 6 weeks of the study intervention (Week 7 to 12). Breaks of up to 30 consecutive days are allowed.

b. Documentation of Acupuncture Visits

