# +/- 3 days to allow flexibility in scheduling of assessments.

^ +/- 7 days to allow flexibility in scheduling of assessments.

$\pi$  After the Week 24 visit, all patients will receive a voucher for 10 free true acupuncture sessions to be administered by the study acupuncturist(s) and used off-study at her convenience.

\* True/Sham acupuncture will be administered twice weekly for 6 weeks (12 sessions) followed by 6 weekly treatments (6 sessions) of maintenance (18 sessions total over 12 weeks).

% Patients on the Waitlist Control arm will not receive any acupuncture (true or sham) until given the vouchers at Week 24. All forms must be submitted as required in Section 14.0.

† Telephone contact at Weeks 2 and 4 will include assessment at adherence to acupuncture, use of pain medications, and adverse events.

~ Telephone contact at Weeks 16 and 20 will include phone administration of the **S1200** Brief Pain Inventory - Short Form (Form #40963) and assessment of use of pain medications.

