#### 11.2 Secondary endpoints:

- a. Secondary hypotheses (Section 10.2) will include assessment of intervention differences at each timepoint individually (weeks 6, 12, 16, 20, 24, and 52), as well as longitudinal modeling of the outcome measures over time. For longitudinal modeling, linear mixed models will be used; if there is evidence of non-random dropout, pattern-mixture models will be utilized as sensitivity analysis. Covariates for longitudinal modeling will include intervention assignment, assessment time, their interaction, baseline score, and other potential confounding variables (*i.e.* age).
- b. Exploratory analyses will also be done to evaluate the relationship between aromatase gene polymorphisms (*CYP19A1*) and inflammatory biomarkers with severity of joint symptoms and response to acupuncture treatment.
- c. A further exploratory analysis at both 6 and 12 weeks according to adherence to intervention assignment will be conducted, with receipt of  $\geq 80\%$  of planned treatment sessions defined as “adherent.” (In particular, patients will be divided into the adherent true ( $\geq 80\%$ ), non-adherent true ( $< 80\%$ ), adherent sham ( $\geq 80\%$ ), and non-adherent sham ( $< 80\%$ ) acupuncture groups.) The interaction between treatment adherence category and treatment category will be tested. Adherence to acupuncture sessions as a continuous measure will also be evaluated.
- d. The success of blinding will be evaluated by using chi-square tests to compare the percentage of patients in each group who believed that they had received true acupuncture at Weeks 6, 12, 24, and 52.

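### Week 52 does not show durability 40 weeks off treatment, and week 12 does not isolate the benefit of maintenance: all arms are offered true acupuncture after week 24, and no arm stops at week 6

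*Protocol*

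**What the plan says.** **Purpose of the visits.** Section 2.0 (Summary) states: "Secondary exploratory endpoints include evaluations at 12, 24, and 52 weeks". It describes weeks 24 and 52 as there "to determine the durability of response 12 and 40 weeks after stopping acupuncture, respectively". That section and Section 1.2 both give week 12 the task "to determine the benefit of additional 6 weekly acupuncture treatments for maintenance". Section 1.2 differs on week 52. It ties durability to week 24 and then says: "The evaluation at 52 weeks is to determine the long-term effects of acupuncture and adherence to AIs".

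**Treatment.** Section 7.6a specifies: "True acupuncture administered twice weekly for 6 weeks followed by weekly treatments for 6 weeks (12-18 sessions total over 12 weeks". The sham arm has the same schedule, and the waitlist arm has no acupuncture before the vouchers. The footnotes to Section 9.0 add: "After the Week 24 visit, all patients will receive a voucher for 10 free true acupuncture sessions". Sections 7.3b and 7.6a leave the use of the voucher to the patient.

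**Analysis.** Section 10.2 lists week 52 among the outcomes on which true acupuncture is compared with sham and waitlist, including AI adherence. Section 11.2a plans "assessment of intervention differences at each timepoint individually (weeks 6, 12, 16, 20, 24, and 52", together with longitudinal models containing arm, time and their interaction. Voucher use is not a named covariate. Section 11.2d compares between groups the percentage of patients "who believed that they had received true acupuncture at Weeks 6, 12, 24, and 52". Section 10.2 also says that use of additional off-study acupuncture will be assessed.

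**The concern.** The Protocol gives two visits a meaning that its own schedule does not support.

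At week 52 both control arms have had access to the tested treatment, and women in the true arm may have resumed it. A small arm difference could mean that the benefit faded or that controls were treated in the meantime. A large one could reflect renewed treatment in the true arm. The AI-adherence comparison at week 52 has the same ambiguity.

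At week 12 a difference between true and control could be reported as evidence that maintenance adds something, although no randomised group went without it.

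The week-52 blinding question has a related weakness. A sham patient who has used vouchers has experienced true needling and can compare it with what she received on study.

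Section 2.0 says that the results are meant to inform clinicians, insurers and patients. How long the effect lasts and whether maintenance is needed are questions these readers would take from the trial.

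**Working it through.** **1. The plan's own intervals.** The last protocol session falls in week 12 (Section 7.6a).
- Week 24: 24 − 12 = 12 weeks.
- Week 52: 52 − 12 = 40 weeks.

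Both stated figures reproduce, counted from the last protocol session.

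**2. What the vouchers change.** Vouchers follow the week-24 visit, so access before the last visit lasts 52 − 24 = 28 weeks (nominal weeks, ignoring visit windows).

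| Arm | Week 24 | Week 52, no voucher used | Week 52, voucher used |
|---|---|---|---|
| True | 12 weeks since last true session | 40 weeks since last true session | 0–28 weeks since last true session |
| Sham | no study true sessions | no voucher true sessions | 0–28 weeks since last true session |
| Waitlist | no study acupuncture | no voucher true sessions | 0–28 weeks since last true session |

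The number of control arms without access to true acupuncture between weeks 24 and 52 is 0. The week-24 column is not affected.

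**3. Week 12.** Let A6 and A12 be the effect of the six-week course over control at weeks 6 and 12, and M the effect added by maintenance.
- True minus control at week 6 = A6.
- True minus control at week 12 = A12 + M, the whole regimen.
- Difference between the two = M + (A12 − A6).

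M separates out only if A12 is known, which needs an arm that stops at week 6. The number of such arms is 0. The change from week 6 to week 12 within the true arm is weaker still, because it also contains any time trend.

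**4. Illustration of size at week 52.** The Protocol gives neither voucher uptake nor a week-52 effect, so this step is assumption throughout. It borrows the week-6 design inputs of Section 11.1: difference 1.7 points, SD 3.0, two-sided α = 0.025, and 104 versus 52 patients with 10% dropout, so 104 × 0.9 = 93.6 and 52 × 0.9 = 46.8.
- Standard error = 3.0 × √(1/93.6 + 1/46.8) = 0.537.
- Power = Φ(1.7/0.537 − 2.241) = Φ(0.92) = 82%, which reproduces the stated week-6 power.

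Suppose that a 1.7-point difference would otherwise remain at week 52 and that voucher use closes a share f of it:

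| f | Contrast, 1.7 × (1 − f) | Power |
|---|---|---|
| 0 | 1.70 | 82% |
| 0.25 | 1.28 | 55% |
| 0.50 | 0.85 | 26% |
| 0.75 | 0.43 | 7% |

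At f = 1 no difference is left to detect. The table shows sensitivity and is not a forecast. It assumes persistence of the effect, which is the question at issue, and it leaves out renewed treatment in the true arm, which could push the contrast the other way.

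**The case against.** The case on the other side is substantial.

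- **The vouchers are optional.** A reader might infer that every control patient has had ten true sessions by week 52. The documents say only that they are offered, and uptake could lie anywhere from none to full.
- **Part of the durability claim is sound.** A reader might conclude that durability cannot be studied at all. Week 24 precedes the vouchers and is a clean randomised comparison 12 weeks after the last session.
- **Section 1.2 is more careful.** It keeps durability for week 24, and its opening frames the secondary objectives as effects of the full course. The 40-week phrase stands only in Section 2.0. However, the claim about maintenance stands in both sections, and deferred access also affects any reading of long-term effects.
- **Off-study acupuncture is recorded**, and Section 10.2 plans to assess it. That permits a non-randomised exploratory look. How it enters a model could properly be left to the SAP.
- **A week-52 intention-to-treat contrast is valid.** A reader might infer that it has to be deleted. It need not be, provided that it is described as what it estimates. Nor does Section 11.2a say outright that the longitudinal model extends to week 52.
- **The blinding item asks about treatment during study participation**, and voucher sessions are off study. That helps, but later true needling can still colour the answer.

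These points narrow the concern. They do not rescue the 40-week claim or the maintenance claim, because an analysis plan cannot supply a missing arm or undo the offer to controls.

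**Conclusion.** The point holds in a limited form. Two stated purposes do not match the design. Week 52 compares early treatment with a deferred offer of true acupuncture, and week 12 estimates the complete 12-week regimen. Both conclusions follow from the schedule alone and need no assumption about uptake. The blinding comparison at week 52 is likewise open to contamination by voucher sessions.

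The amount of distortion at week 52 cannot be derived from the documents, and the dilution table should not be cited as an estimate. The documents also do not support the stronger reading that neither durability nor maintenance can be examined in any way. Week-24 durability is intact, and non-randomised exploratory analyses remain possible. The week-6 primary analysis, its α and the sample size are unaffected. Severity is moderate, because these are secondary endpoints that Section 2.0 calls exploratory.

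**What to change.** - **Sections 1.2 and 2.0:** describe week 12 as the effect of the complete 12-week regimen against each control. Limit the durability claim to week 24, and remove the 40-week statement from Section 2.0 so that the two sections agree.
- **Sections 10.2 and 11.2a:** name week 24 as the last comparison before voucher access. Keep week 52, including AI adherence, only as an exploratory intention-to-treat contrast labelled early versus deferred offer of true acupuncture. Report beside it, by arm, the off-study sessions already being recorded.
- **Section 11.2d:** remove week 52 from the blinding test and keep weeks 6, 12 and 24.

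The cost is wording and analysis scope. Visits, vouchers, forms and sample size stay as they are. The price is giving up a claim of durability off treatment at 52 weeks, which the design does not support.
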